**Methods/Design:**

Patients diagnosed with CTS will be recruited from an outpatient neurology clinic and randomly assigned to the intervention group (mechanical traction) or the control group (care as usual). Participants in the intervention group will receive 12 treatments with mechanical traction during six consecutive weeks. Primary outcome is symptom severity and functional status, which are measured with the Boston Carpel Tunnel Questionnaire (BCTQ). Secondary outcomes are quality of life (WHOQOL-BREF), health related resource utilization, and absenteeism from work. Outcomes will be assessed at baseline, and at 3, 6, and 12 months after inclusion. Linear mixed effect models will be used to determine the change from baseline at 12 months on the BCTQ, WHOQOL-BREF, absenteeism from work and health related resource utilization. The baseline measurement, change from baseline at three and six months, as well as duration of symptoms until inclusion, age, gender, and co-morbidity will be included as covariates The Pearson’s correlation coefficient will be generated to assess the correlation between depression and anxiety and treatment outcome.

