### Hypothesis and objectives

The purpose of this study is to evaluate the effectiveness of mechanical traction in alleviating symptoms and improving hand function in patients with CTS compared to care as usual. The primary outcome is the change from baseline in symptom severity and functional status at 12 months, which is measured using the Boston Carpal Tunnel Questionnaire (BCTQ). Change from baseline in functional status and symptom severity at three and six months will be used as covariates. As secondary outcomes, we will assess quality of life, health related resource utilization, and absenteeism from work. Tertiary outcome is the impact of psychological distress on treatment outcome. We hypothesize that hand function and symptom severity will significantly improve more in CTS patients receiving 12 treatments with mechanical traction compared to CTS patients who receive care as usual after 12 months. Moreover, 12 treatments with mechanical traction will result in less absenteeism from work, a higher quality of life, and less health related resource utilization compared to care as usual in CTS patients after 12 months follow-up. Furthermore, a higher degree of depression and anxiety at baseline will result in a lower treatment effect in CTS patients.

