### Tertiary outcome measures

#### Depression and anxiety

The four-item Patient Health Questionnaire (PHQ-4) will be used to measure self-reported depression and anxiety. The questionnaire consists of two items on depression and two on anxiety, referring to the past two weeks. A higher score represents a higher level of anxiety and depression. The PHQ-4 is a reliable instrument that has been validated in a general population [26].

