#### Planned analyses

The baseline characteristics of those who complete and will drop out during follow-up will be compared by means of an independent *t*-test for continues data and by Chi square analysis for categorical data. All analyses will be based on the intention-to-treat principle. Linear mixed effect models will be used to compare the change from baseline at 12 months between groups on the BCTQ, WHOQOL-BREF, absenteeism from work and health related resource utilization. Linear mixed effect models are able to adjust for missing values and are therefore used to avoid loss of information [27]. The baseline, three and six months measurements, as well as duration of symptoms until inclusion, age, gender, and co-morbidity will be included as covariates. Taking these covariates into account will adjust for differences within the groups and decrease variance. It will also adjust for possible baseline differences between groups [28]. When the data are normally distributed, Pearson’s correlation coefficients will be generated to examine the relationship between treatment outcome and depression and anxiety.

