## Discussion

This paper describes the design for an RCT with the purpose to study the effectiveness of mechanical traction as a treatment for CTS compared to care as usual. Recruitment started in October 2013 in the VieCuri Medical Center in Venlo, The Netherlands. The outpatient neurology clinic registers over 400 CTS patients annually of whom about 350 will be eligible. During a period of 12 months, these patients will be invited to participate in the RCT. For several reasons, it is realistic to predict a response rate of 60%. First, the new treatment is painless and non-invasive. Second, in case of a non-responder, the patient can always make a choice for surgery without any evidence for poorer prognosis. The predicted sample size of 200 patients will easily enable the researchers in one year to include sufficient patients into the trial with sufficient power. The clinical relevance of this RCT is substantial. First, CTS is very common, not only in the general population (up to 4%), but especially in the working population (up to 10%). Secondly, because the prevalence in the working population is relatively high, CTS-related days of sick leave and workers’ compensation lead to an economic burden. Absenteeism from work after carpal tunnel release (CTR) is on average two to seven weeks [29,30]. In the US, cumulative excess loss of earnings of 4,443 workers who filed a CTS related workers’ compensation claim was estimated at $197 to $382 million over 6 years [31]. Thirdly, the long-term benefits of current treatment strategies of CTS are far from optimal. Fourth, it is well known that recovery from pain symptoms can be mediated by the patient’s mental state, especially anxiety and depression. Pain is a process from nociceptive registration to a subjective experience, which can be influenced by psychological wellbeing [32]. Depression has been reported as a predictor of pain intensity in CTS patients [6]. Research into the mediator effect of emotional distress on the outcome of CTS treatment is limited. Hobby *et al*. reported a significant association between BCTQ scores and scores on the depression and anxiety scales [33]. Moreover, Lozano Calderon *et al*. reported that patient dissatisfaction and perceived impairment after CTR can partly be predicted by depression [34]. Up until now, non-invasive CTS treatment mostly consists of splint therapy and corticosteroid injections. These treatments have not been proven to be effective in the long-term [8-10]. Invasive CTR, on the other hand, results in a positive outcome in only 70 to 75% of the patients in the long-term [16,17]. Mechanical traction using the Phystrac traction device is a promising treatment option. It is non-invasive and has been reported to result in substantial symptom relief in 70% of the patients, and in 60% of the patients two years post-treatment [19,20]. However, there is no conclusive scientific evidence for the effectiveness of mechanical traction. Therefore, there is a clear need for an RCT to compare mechanical traction to regular treatment options, such as splint therapy, steroid injections, and CTR. Improvements in functional status and symptom severity will be measured using the BCTQ. This questionnaire has been proven to be a valid and reliable outcome measure [21,22]. It is widely used in clinical practice to evaluate the recovery of CTS symptoms after treatment. This means that we have an easy, user-friendly, and quick measure to assess clinical outcome. One strength of this study is the additional outcome measures. Apart from clinical measures, quality of life, absenteeism from work, and health related resource utilization will be measured. Another strength of this study is the follow-up length. Many studies only include a few weeks or months follow-up, while the current study aims at a 12 months follow-up period. A possible limitation of this study is the heterogeneity of the care as usual group. The patients in this group can receive different forms of treatment or no treatment at all. However, since this represents the general practice in an outpatient neurology clinic, the results of this RCT will provide clinically relevant information.

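### The hypothesis that baseline distress lowers the treatment effect is paired only with a distress–outcome correlation, which cannot show effect modification and could be misread as doing so

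*Protocol article*

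**What the plan says.** Under Hypothesis and objectives, the last hypothesis is that "a higher degree of depression and anxiety at baseline will result in a lower treatment effect in CTS patients". The same section words the objective more loosely: "Tertiary outcome is the impact of psychological distress on treatment outcome".

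Under Planned analyses, subject to normality, Pearson's "correlation coefficients will be generated to examine the relationship between treatment outcome and depression and anxiety". The Abstract says the same: Pearson's "coefficient will be generated to assess the correlation between depression and anxiety and treatment outcome". Neither place says whether the correlation is pooled or by arm, or which distress measurement is used.

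The measure is named under Tertiary outcome measures: "The four-item Patient Health Questionnaire (PHQ-4) will be used to measure self-reported depression and anxiety". Table 1 schedules it at every time point, including baseline (T0).

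The mixed-model covariates are the baseline, three- and six-month measurements, "as well as duration of symptoms until inclusion, age, gender, and co-morbidity will be included as covariates". PHQ-4 is not among them, and no interaction of PHQ-4 with group is stated.

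The Discussion adds a third notion: "Research into the mediator effect of emotional distress on the outcome of CTS treatment is limited".

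**The concern.** A treatment effect in a randomised comparison is a contrast between the arms. To say that it is lower in more distressed patients is to say that this contrast depends on baseline PHQ-4. A correlation between distress and outcome contains no such contrast. It shows whether distressed patients do worse, not whether traction helps them less relative to usual care.

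The distinction matters here because the article itself leads the reader to expect a prognostic association: "Depression has been reported as a predictor of pain intensity in CTS patients". It also cites an association of BCTQ scores with depression and anxiety scores, and prediction by depression of impairment after surgery, which is one of the usual-care options. A correlation may therefore appear even if traction works equally well at all levels of distress. Read against the stated hypothesis, it could be reported as evidence that distress weakens the treatment.

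The method is stated, and stated twice, so this is not a detail held over for the analysis plan.

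**Working it through.** **The plan's own figure.** For d = 0.5, two-sided alpha 0.05 and power 0.8, n per arm = 2(1.960 + 0.842)²/0.5² = 62.8, so 63. The t-test calculation gives 63.8, so 64, as stated in the protocol. The point does not depend on this figure. It supplies the two totals used below: 128 (2 × 64) and the planned 200.

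**What each statistic estimates.** Let y be improvement, X standardised baseline PHQ-4 and G the group (1 = traction):

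y = α + δG + βX + γGX + error.

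The treatment effect at distress x is δ + γx, so the hypothesis is γ < 0. With 1:1 allocation the pooled slope of y on X is β + γ/2. Within traction it is β + γ, and within usual care it is β. None of these is γ. If distress is only prognostic (γ = 0, β < 0), all three are negative.

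**Chance of a significant correlation when γ = 0.** By Fisher's z:

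Φ(atanh(r)·√(N−3) − 1.96) + Φ(−atanh(r)·√(N−3) − 1.96).

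Example, r = 0.2 and N = 200: 0.2027 × 14.04 = 2.85, and Φ(2.85 − 1.96) = 0.81. The values of r (size of the correlation) are assumptions, because the documents give none.

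| assumed r | pooled, N = 200 | pooled, N = 128 | one arm of 100 | one arm of 64 |
|---|---|---|---|---|
| 0.1 | 29% | 20% | 17% | 12% |
| 0.2 | 81% | 62% | 51% | 35% |
| 0.3 | 99% | 93% | 86% | 68% |

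A simulation (5,000 trials per scenario, d = 0.5 between arms) counted only significant results in the hypothesised direction. The pooled figures were 28%, 79% and 99% at N = 200, and 19%, 61% and 91% at N = 128. The group × distress interaction test rejected in about 5% (4.5% to 5.5%) throughout. Restricting the correlation to the traction arm lowers the figures but does not remove the problem.

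**One correlation, two truths (N = 200, simulated).** Both rows have a pooled slope of −0.2.

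| truth | pooled correlation significant, hypothesised direction | interaction test significant |
|---|---|---|
| prognostic only: slope −0.2 in both arms | 79% | 5% |
| modification: slope −0.4 in traction, 0 in usual care | 76% | 80% |

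The correlation behaves almost identically in the two cases. The interaction test separates them.

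**What the interaction test can deliver.** With outcome residual and PHQ-4 in SD units, SE(γ) ≈ 2/√N, which is 0.141 at N = 200 and 0.177 at N = 128.
- Slope difference 0.4, N = 200: 0.4/0.141 = 2.83, and Φ(2.83 − 1.96) = 0.81.
- Slope difference 0.2, N = 200: 0.2/0.141 = 1.41, and Φ(1.41 − 1.96) = 0.29.
- At N = 128 the same steps give about 62% and 20%.
- The 95% CI half-width is 1.96 × 0.141 = 0.28 at N = 200 and 1.96 × 0.177 = 0.35 at N = 128.

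**The case against.** The strongest reply is that the hypothesis was meant prognostically. The Background uses the term treatment effect for a benefit that wears off in patients given injections, with no comparator. The two preceding hypotheses name usual care as comparator, and the distress hypothesis does not. The tertiary outcome is worded as impact on outcome, and the evidence cited in the Discussion concerns association and prediction. For that question a correlation is crude but legitimate. This stands as a limit on the point. It does not remove the explicit hypothesis of a lower treatment effect, which sits in the same section. If prognosis is what was meant, that sentence needs rewording.

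A reader might go further and infer that the correlation will give a false claim whenever distress is prognostic. The documents do not support that. The chance of significance depends on the strength of the association and on N, and is only 20% to 29% at r = 0.1. A significant correlation would also be a true prognostic result. It becomes a wrong claim only if reported as a lower treatment effect, and Planned analyses sets no rule for declaring the hypothesis supported or refuted.

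A reader might also infer that the correlation would hide real modification. Slopes of opposite sign in the two arms can cancel, but that requires distressed usual-care patients to do better, against the evidence the article cites. The point does not rest on it.

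It is likewise not stated that the correlation is pooled, which is why one-arm figures are shown. Nor is the normality condition a fault here: the fallback can be left to the analysis plan.

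**Conclusion.** The point holds as a mismatch between a stated hypothesis and a stated method. The hypothesis most naturally describes effect modification. The planned correlation, pooled or within one arm, cannot show it, and no PHQ-4 by group term is stated.

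If distress is only prognostic, a significant correlation open to misreading has a chance of about 29%, 81% or 99% (N = 200) for r = 0.1, 0.2 or 0.3, and 20%, 62% or 93% (N = 128). An interaction test would stay near 5%. These figures rest on assumed correlations, roughly normal scores and complete data for the stated N.

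The article mixes prognosis, moderation and mediation for this objective, and the passages should be reconciled. The objective is tertiary. The sample size and the primary conclusion are not affected.

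**What to change.** Choose one of two courses.

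1. If effect modification is meant, add baseline (T0) PHQ-4 as a continuous variable, and its interaction with group, to the 12-month BCTQ model. Report the interaction with a 95% CI. Keep the correlation or the PHQ-4 main effect as a prognostic description only.
2. If only prognosis is meant, restate the hypothesis as an association of baseline distress with outcome, and drop the reference to a lower treatment effect.

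In either case, name T0 as the distress measurement and align the wording in Hypothesis and objectives, the Abstract, Planned analyses and the Discussion.

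The cost is wording and two model terms, using data already scheduled at T0. The downside of the first course is limited power: about 80% at N = 200 only for a slope difference near 0.4 SD per SD of PHQ-4, and about 29% for 0.2 SD. The interaction should therefore be presented as exploratory, and a non-significant result should not be read as absence of modification.

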### Primary outcome measure

#### Functional status and symptom severity

Self-reported functional status and symptom severity will be measured using the BCTQ [21,22]. The BCTQ is a disease-specific questionnaire referring to a typical 24-hour period in the past two weeks. It consists of two different scales: the Symptom Severity Scale (SSS) and the Functional Status Scale (FSS). The SSS comprises 11 questions about symptom severity, while the FSS consists of 8 daily activities which are rated based on degree of difficulty. The SSS and the FSS will be rated on a five-point scale. Both scales result in mean scores between 1 and 5, where greater impairment is represented by higher scores. The BCTQ is responsive to clinically relevant change and therefore an appropriate measure for treatment outcome [21]. It has been validated and is used in multiple studies to assess improvement in CTS symptoms over time [14], and also in The Netherlands [13,23].

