## Statistical analysis

### Sample size and power calculation

The sample size calculation is based on a clinically relevant improvement from baseline on the functional and symptom severity scores of the BCTQ after 12 months follow-up. Sixty-four patients need to be included per treatment arm to statistically detect a minimum effect size of *d* = 0.5 between mean BCTQ scores of both groups with a power of 0.8 and a two-sided alpha of 0.05. A total of 200 patients will be included (100 patients per treatment arm), taking into account possible drop-out.

The following outcomes are defined. A completer is a patient who participated in at least 70% of the intervention sessions and the assessments. A responder is a patient who will have a reduction of 0.74 of the mean score (minimal clinical important difference) on the BCTQ compared to baseline [21]. A drop-out is a patient with less than 70% of the intervention or the follow-up data.

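### The tertiary distress analysis is an unadjusted Pearson correlation with an unspecified outcome, so it cannot separate an influence of distress from baseline severity

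*Protocol article*

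**What the plan says.** Under Planned analyses, the tertiary question is to be answered, if the data are normal, by Pearson "correlation coefficients will be generated to examine the relationship between treatment outcome and depression and anxiety". The abstract names the same method. Neither place says whether the outcome is the change in BCTQ or the 12-month score.

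The covariate sentence stands just before, after the description of the mixed models: "The baseline, three and six months measurements, as well as duration of symptoms until inclusion, age, gender, and co-morbidity will be included as covariates". It belongs to those models; nothing extends it to the correlation.

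Three other statements bear on the point:

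- Hypothesis and objectives expects that "a higher degree of depression and anxiety at baseline will result in a lower treatment effect in CTS patients".
- The same section defines the main outcome on the change scale: "The primary outcome is the change from baseline in symptom severity and functional status at 12 months".
- The Discussion cites an earlier study that "reported a significant association between BCTQ scores and scores on the depression and anxiety scales". It gives neither the size of that association nor its time point.

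On direction, for the BCTQ "greater impairment is represented by higher scores", and for the PHQ-4 "A higher score represents a higher level of anxiety and depression".

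**The concern.** Treatment groups are randomised; distress levels are not. If distressed patients tend to enter with higher BCTQ scores, as the cited association suggests, any raw correlation of PHQ-4 with a later BCTQ measure carries that starting difference with it.

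The way it does so depends on the outcome chosen. Change contains the baseline score with a negative sign, so patients who start higher have more room to fall and may regress further. Distress can then look helpful. The 12-month score contains the baseline score with a positive sign, so distress can look harmful. One planned sentence therefore allows two analyses that baseline severity can pull in opposite directions. At stake is the direction of the tertiary conclusion, not the comparison of traction with usual care.

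**Working it through.** **The plan's own figure.** The only computable figure in the article is the sample size: d = 0.5, "with a power of 0.8 and a two-sided alpha of 0.05". The normal approximation gives 2 × (1.960 + 0.842)² / 0.5² = 62.8, so 63 per arm; the t-test solution is 63.77, so 64. The stated 64 is reproduced. It serves the group comparison; no figure is stated for the correlation. I use N = 128 (2 × 64) and N = 200 (planned enrolment) as the two sizes.

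**Assumed inputs (none is in the article).**
- q = correlation of baseline PHQ-4 with baseline BCTQ
- r = correlation of baseline with 12-month BCTQ
- k = SD at 12 months divided by SD at baseline

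**Scenario A: distress is independent of 12-month BCTQ given baseline BCTQ.**

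Correlation with change (12 months minus baseline) = q(kr − 1)/√(1 + k² − 2rk). For k = 1 this is −q√((1 − r)/2), which at r = 0.5 is −0.5q. Correlation with the 12-month score = qr, which at r = 0.5 is +0.5q.

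The chance of two-sided p<0.05 comes from Fisher's z with standard error 1/√(N − 3). Example with q = 0.3 and N = 200: atanh(0.15) = 0.151; 0.151 × √197 = 2.12; Φ(2.12 − 1.96) = 0.56.

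| q (r = 0.5, k = 1) | Corr. with change | Corr. with 12-month score | p<0.05, N = 128 | p<0.05, N = 200 |
|---|---|---|---|---|
| 0.2 | −0.10 | +0.10 | 20% | 29% |
| 0.3 | −0.15 | +0.15 | 39% | 56% |
| 0.4 | −0.20 | +0.20 | 62% | 81% |

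At r = 0.5 and k = 1 the two correlations have equal size, so the rates apply to both outcomes. A negative correlation with change means a larger fall with more distress, against the hypothesis; a positive one with the 12-month score agrees with it. Simulation (5,000 runs per setting) gave the same rates to within about one percentage point. The partial correlation given baseline was significant in 4.3% to 5.5% of runs.

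The result is sensitive to the assumptions. With k = 1, q from 0.1 to 0.5 and r from 0.3 to 0.7, the rate for change runs from 7% to 93% at N = 128 and from 8% to 99% at N = 200. At q = 0.3, r = 0.5 and N = 200, it is 80% for k = 0.8 and 28% for k = 1.25.

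**Scenario B: distress has the same correlation q with BCTQ at both times (k = 1).**

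The covariance with change is q − q = 0. In simulation the raw correlation with change averaged zero and was significant in about 5% of runs. The partial correlation given baseline is now q(1 − r)/√((1 − q²)(1 − r²)):
- q = 0.2, r = 0.5: 0.10/√(0.96 × 0.75) = 0.12
- q = 0.4, r = 0.4: 0.24/√(0.84 × 0.84) = 0.29

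Both are in the hypothesised direction. At r = 0.5 the partial correlation was significant in 25%, 54% and 83% of runs at N = 128, and 37%, 73% and 95% at N = 200, for q = 0.2, 0.3 and 0.4.

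**The case against.** The strongest reply is that neither analysis is simply right. If distress goes with stable severity, and baseline and 12-month scores are noisy readings of that severity, raw change is uncorrelated with distress, and it is the baseline-adjusted analysis that shows an association. This is Lord's paradox: in a non-randomised comparison, change and baseline-adjusted analyses answer different questions. The objection stands, and it limits the point in two ways.

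- A reader might infer that regression to the mean will make the planned correlation significant with the wrong sign. The article does not support that. It gives none of q, r or k, does not say at what time distress and BCTQ were associated, and does not fix change as the outcome of the correlation. Scenario B gives no such bias.
- A reader might infer that baseline adjustment always restores a 5% error rate. It does so in scenario A, where the data follow the model being fitted, but not in scenario B.

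The same data can even fit both descriptions. Let 12-month BCTQ = b × baseline + g × distress + error, with unit variances, b = 0.5, q = 0.3 and a real adverse influence g = 0.15. The covariance with change is g − (1 − b)q = 0.15 − 0.15 = 0, and that with the 12-month score is bq + g = 0.30 = q. That is scenario B. Patients with more distress then do worse than others who start at the same score, yet the raw change correlation centres on zero.

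It can also be said that a condensed article may leave the definition of the outcome to an analysis plan not shown. That is fair for the definition alone. But the method itself is named, in the abstract and in the analysis section, without adjustment.

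Finally, the question is labelled tertiary, and no error rate or decision rule is attached to it; the 0.05 belongs to the group comparison. That limits the weight of the point.

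**Conclusion.** The point holds in a limited form. The planned raw correlation cannot distinguish an influence of distress from baseline severity, and baseline can pull it either way depending on which outcome is used. Under scenario A with q of 0.2 to 0.4, r = 0.5 and equal SDs, p<0.05 would occur in about 20% to 62% of trials at N = 128 and 29% to 81% at N = 200. Under scenario B the change correlation is centred on zero. The article does not show which scenario applies, so these rates show what is possible and are not a forecast.

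Baseline adjustment is still the better main analysis. The hypothesis concerns the influence of baseline distress on the result of treatment, and the sponsor already adjusts for baseline in its other models. This is a cheap improvement to a tertiary analysis. Nobody should read it as a flaw in the primary or secondary comparisons, whose models include the baseline measurement.

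**What to change.** Replace the correlation sentence with one that:

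1. defines the outcome as 12-month SSS and, separately, 12-month FSS;
2. regresses each on baseline PHQ-4, adjusting for the baseline value of the same scale, treatment arm, age, gender, symptom duration and co-morbidity;
3. reports the PHQ-4 coefficient with its 95% CI;
4. reports the unadjusted association of PHQ-4 with change as a sensitivity analysis, and states that the two answer different questions.

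There is one downside to state openly. When baseline severity is measured imperfectly, the adjusted coefficient can keep residual confounding in the hypothesised direction. Both results should therefore be shown, and neither read as causal.

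The cost is a few lines in the analysis section. Table 1 already schedules the BCTQ and PHQ-4 at baseline and 12 months, so no extra patients, visits or questionnaires are needed.
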